## Abstract

**Background:** Sepsis commonly causes acute respiratory distress syndrome (ARDS), and ARDS contributes to poor prognosis in sepsis patients. Early prediction of ARDS for sepsis patients remains a clinical challenge. This study aims to develop and validate chest computed tomography (CT) radiomic-based signatures for early prediction of ARDS and assessment of individual severity in sepsis patients. **Methods:** In this ambispective observational cohort study, a deep learning model, a sepsis-induced acute respiratory distress syndrome (SI-ARDS) prediction neural network, will be developed to extract radiomics features of chest CT from sepsis patients. The datasets will be collected from these retrospective and prospective cohorts, including 400 patients diagnosed with sepsis-3 definition during a period from 1 May 2015 to 30 May 2022. 160 patients of the retrospective cohort will be selected as a discovering group to reconstruct the model and 40 patients of the retrospective cohort will be selected as a testing group for internal validation. Additionally, 200 patients of the prospective cohort from two hospitals will be selected as a validating group for external validation. Data pertaining to chest CT, clinical information, immune-associated inflammatory indicators and follow-up will be collected. The primary outcome is to develop and validate the model, predicting in-hospital incidence of SI-ARDS. Finally, model performance will be evaluated using the area under the curve (AUC) of receiver operating characteristic (ROC), sensitivity and specificity, using internal and external validations. **Discussion:** Present studies reveal that early identification and classification of the SI-ARDS is essential to improve prognosis and disease management. Chest CT has been sought as a useful diagnostic tool to identify ARDS. However, when characteristic imaging findings were clearly presented, delays in diagnosis and treatment were impossible to avoid. In this ambispective cohort study, we hope to develop a novel model incorporating radiomic signatures and clinical signatures to provide an easy-to-use and individualized prediction of SI-ARDS occurrence and severe degree in patients at early stage.

## 1. Introduction

Sepsis-induced acute respiratory distress syndrome (SI-ARDS) is a common and severe complication of sepsis and is an independent contributor to poor prognosis of patients [1,2]. Acute respiratory distress syndrome (ARDS) is characterized by lung epithelial injury with a decrease of oxygenation index and is manifested as respiratory distress [3]. Once injury to the lung epithelial damage is evidently promoted, the progression to ARDS cannot be reversed, and the mortality rate reaches approximately 40% [4,5]. However, it remains a clinical challenge to identify SI-ARDS early and accurately, something which could optimize treatment strategy and reduce the mortality risk [6]. As such, a novel method for early identification of SI-ARDS is of paramount interest to clinicians and researchers.

Immune dysfunction driving sepsis-induced target organ damage has been fully appreciated and is characterized by excessive inflammatory reaction and immune function inhibition [7,8]. However, despite much significant research that has been undertaken to improve the understanding of ARDS pathogenesis, including viable predictive molecular biomarkers and multigene-based expression assays, early identification for SI-ARDS remains elusive [9,10,11,12,13]. Additionally, the immune microenvironment, influenced by the above mechanisms, has not been quantitatively assessed for the early identification of SI-ARDS, which comprises immune cell subsets, inflammatory cytokine and other components [14,15,16]. Recent studies have revealed artificial intelligence with radiomics emerging as a quantitative imaging method for early detection, risk assessment, and treatment decisions in various diseases [17,18]. Despite the lack of a clear correlation between radiomics and pathophysiology, application of radiomics in predicting SI-ARDS is worth exploring.

Computerized tomography (CT) of the chest is easily accessible for patients in order for the identification of pulmonary or non-pulmonary sepsis and is also a method for ARDS diagnosis based on characteristic radiologic features. Also, radiomic high-dimensional features extracted from CT images offer an insight into microvascular injury of SI-ARDS, which are imperceptible to human eyes and relevant to intra-alveolar heterogeneity and potential prognosis. Herein, we used a single center ambispecive cohort study to develop a radiomics classification model and demonstrated the robust correlation between radiologic features and SI-ARDS occurrence. Further, we established a prediction model integrating radiomics and clinicopathological characteristics for more precise prediction of ARDS severity.

## 2. Materials and Methods

### 2.1. Study Design

The study was registered with ClinicalTrials.gov (NCT04541264, https://clinicaltrials.gov/show/NCT04541264) on 9 September 2020. In this double-center, ambispective, observational study, we will collect chest CT and clinical information of patients with sepsis and septic shock treated in our hospital (Sun Yat-sen Memorial Hospital, Sun Yat-sen University) and Shenshan Medical Center, Memorial Hospital of Sun Yat-sen University (from 1 May 2015 to 30 May 2022). For the final analysis, 400 patients will be enrolled according to the TRIPOD guideline [19]. Among the 400 patients, 200 will be retrospectively recruited from our hospital from May 2015 to August 2020, 100 patients will be prospectively recruited from our hospital from August 2020 to May 2022, and the other 100 patients will be prospectively recruited from Shenshan Medical Center, Memorial Hospital of Sun Yat-sen University from August 2020 to May 2022. One hundred-sixty patients of the retrospective cohort will be selected as a discovering group to reconstruct the model, and 40 patients of the retrospective cohort will be selected as a testing group for internal validation. Additionally, 200 patients of the prospective cohort will be selected as a validating group for external validation. Follow-up of the relevant patients will be conducted until April 2023. This study was approved on 19 August 2020 by the Ethics Committee of Sun Yat-sen Memorial Hospital, Sun Yat-sen University, Guangzhou, China. Figure 1 shows the flow chart of the study protocol.

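### The 200-patient group labelled external validation is half temporal validation at the development hospital; only the 100 Shenshan patients test the model at another site

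*Protocol article*

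**What the plan says.** Section 2.1 (Study Design) of the protocol article sets out 400 patients in three blocks:

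- Retrospective, home hospital: "200 will be retrospectively recruited from our hospital from May 2015 to August 2020". This block supplies the 160 discovering patients and the internal test set ("40 patients of the retrospective cohort will be selected as a testing group for internal validation").
- Prospective, home hospital: "100 patients will be prospectively recruited from our hospital from August 2020 to May 2022".
- Prospective, second site: "the other 100 patients will be prospectively recruited from Shenshan Medical Center, Memorial Hospital of Sun Yat-sen University from August 2020 to May 2022".

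The two prospective blocks are then joined under one label: "200 patients of the prospective cohort will be selected as a validating group for external validation". The Abstract says the same and mentions both sites: "200 patients of the prospective cohort from two hospitals will be selected as a validating group for external validation". Section 2.2 again speaks of a single validating group of 200.

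The Abstract names AUC, sensitivity and specificity as the measures for internal and external validation. Section 2.7 (Statistical Analysis) lists two subgroup comparisons, by septic shock and by pulmonary source of sepsis. Site is not among them.

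**The concern.** External validation asks whether a model keeps its performance where it was not built. The 100 prospective home-hospital patients differ from the development set in calendar period and mode of collection, but not in hospital. They are a sound temporal validation, and they cannot show that the model transports to another hospital. Only the Shenshan patients can.

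Site is a plausible source of failure for a CT-based network. Section 2.5 itself notes that scans are made with varying equipment and settings, and the Discussion says that referral to CT depends on perceived risk. If performance falls at Shenshan, the home-hospital half dilutes the fall in any figure for the combined 200, and the interval around that figure reflects twice the number of patients who bear on the question. A reader would then credit the model with more transportability, and more certainty about it, than the data give.

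**Working it through.** **1. Cohort counts (2.1).** 200 + 100 + 100 = 400, which reproduces the stated total. Development: 160 + 40 = 200, all from the home hospital. Validation: 100 + 100 = 200, which reproduces the stated group size. Share of the validation group from the development hospital: 100/200 = 50%.

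**2. Expected ARDS cases.** Section 2.3 gives a 25–50% occurrence rate. The combined 200 would contain 50–100 cases; the Shenshan 100 would contain 25–50.

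**3. Precision.** The documents state no expected AUC, so 0.80 is an assumption. The Hanley–McNeil standard error, with n₁ cases and n₀ non-cases, is

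SE² = [A(1−A) + (n₁−1)(Q₁−A²) + (n₀−1)(Q₂−A²)] / (n₁n₀), with Q₁ = A/(2−A) and Q₂ = 2A²/(1+A).

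At A = 0.80, Q₁ = 0.6667 and Q₂ = 0.7111, so Q₁−A² = 0.0267 and Q₂−A² = 0.0711. For 25 cases and 75 non-cases: (0.16 + 24×0.0267 + 74×0.0711)/1875 = 0.00324, so SE = 0.057.

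| Set | Cases / non-cases | SE | 95% half-width |
|---|---|---|---|
| Shenshan, 100 | 25 / 75 | 0.057 | 0.11 |
| Shenshan, 100 | 50 / 50 | 0.045 | 0.09 |
| Combined, 200 | 50 / 150 | 0.040 | 0.08 |
| Combined, 200 | 100 / 100 | 0.031 | 0.06 |

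The ratio is 0.0569/0.0401 = 1.42 at 25% ARDS and 0.0445/0.0314 = 1.42 at 50%, as expected from √2. Over assumed AUCs of 0.70–0.85, the half-width is 0.08–0.13 for 100 patients and 0.05–0.09 for 200.

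**4. Masking.** Assume equal ARDS rates at the two equal-sized sites and an equal-variance binormal score. True AUCs of 0.82 (home) and 0.72 (Shenshan) pool to 0.770 if non-cases score alike at both sites, and to 0.772 if the scores are centred at each site. Either way the result is about 0.77, so half of the 0.10 drop is hidden. With 0.85 and 0.65 the pooled value is about 0.75–0.76.

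**5. Cross-site pairs.** An AUC is the proportion of case/non-case pairs ranked correctly. With two equal sites and equal ARDS rates, half of the pairs in the combined group set a case at one site against a non-case at the other.

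- With equal ARDS rates, a shift in score level between sites only lowers the pooled AUC in this model: 0.80 becomes 0.793 at a shift of 0.5 SD and 0.773 at 1 SD.
- With unequal rates it can move either way. Take the two ends of the 25–50% range, one at each site, and a score that recognises only the site. Pairs: 75 cases × 125 non-cases = 9375, of which 50×75 = 3750 are ordered correctly and 25×75 + 50×50 = 4375 are ties. The AUC is (3750 + 0.5×4375)/9375 = 0.63, although it is 0.50 within each site. With the direction reversed it is (1250 + 0.5×4375)/9375 = 0.37. This is an extreme case. For a score with a within-site AUC of 0.80 and a 1 SD shift aligned with the higher rate, the pooled value is about 0.82.

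**The case against.** The strongest reply is that the article never says that one pooled figure will be the only result. It is a condensed account, the analysis plan is not shown, and tabulation by site is something such a plan commonly contains. That stands: a reader might infer that by-site results are ruled out, and the documents do not support this. What the article does fix is the label and the group definition, and for half of the group the label is wrong whatever the analysis plan adds.

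A reader might also infer that the study cannot support any claim of external validity. That goes too far. One hundred patients do come from a second hospital, the home-hospital 100 are later patients not used for development, the composition is openly disclosed, and the Discussion calls the data inconclusive and asks for further multicenter validation. However, its limitations (selection, short follow-up, sample size and overfitting) do not mention that half of the validation group shares the development hospital.

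Three further limits are accepted:

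- Nothing in the documents shows that care pathways or CT referral at the home hospital stayed the same between the two periods. The point needs only the shared hospital.
- Inflation of a pooled AUC requires both ARDS rates and score levels to differ by site, and no site-specific rates are given.
- In the 0.82 versus 0.72 example, reporting by site would often not establish the difference. Its standard error is 0.066–0.084, so z is about 1.2–1.5 and power about 22–33% at the two-sided 5% level. Separate reporting shows the second-site result honestly; it does not guarantee a significant contrast.

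The Introduction's description of a single-center study ("we used a single center ambispecive cohort study to develop a radiomics classification model"), against the double-center wording in 2.1, is a separate editorial matter, since development is indeed at one hospital. Nothing here rests on it.

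**Conclusion.** The point holds as a fault of labelling and reporting, not of the data. Half of the group called external (100 of 200) comes from the only hospital that supplies development data. For that group as defined, a performance figure would mix temporal with geographic validation, hide about half of any drop at the second site, and overstate the precision of the external evidence by a factor of about 1.4.

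The counts and the factor of 1.4 follow from the article's own numbers. The absolute standard errors rest on an assumed AUC of 0.80 and the article's 25–50% ARDS rate; the masking example rests on assumed site AUCs, equal ARDS rates and a binormal score. Distortion from cross-site pairs is possible but conditional, and its size cannot be judged from the documents. The change should be made before results are reported, because it determines which figure carries the external claim.

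**What to change.** In 2.1, 2.2 and the Abstract, call the 100 prospective home-hospital patients the temporal validation set and the 100 Shenshan patients the external (geographic) validation set. State that the claim of external validity rests on Shenshan. Report AUC, sensitivity and specificity with 95% confidence intervals for each site. If a combined AUC is also given, build it from within-site pairs only and present it as a summary over both sets, not as the external result.

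No extra patients or data are needed: the cost is a change of wording and one analysis by site. The downside is a wider external interval (about ±0.09 to ±0.11 at AUC 0.80, against ±0.06 to ±0.08 for the combined 200), and the text should say that a modest difference between sites may well not reach significance.

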### 2.2. Cohort Descriptions and Definitions

This study will recruit 200 patients in a developing group and 200 patients in a validating group from two hospitals. Patients’ age above 18 years diagnosed as sepsis or septic shock will be screened for eligibility. SI-ARDS is defined by sequential occurrence of the sepsis-3 consensus criteria for sepsis [7] and the Berlin definition for ARDS [2]. Exclusion criteria are (1) admission stay <24 h, (2) patients with end-stage lung disease or long-term oxygen therapy, (3) patients with sepsis or septic shock whose oxygenation index (OI, arterial oxygen tension/inspired oxygen fraction [PaO2/FIO2]) ≤300 mmHg before admission, (4) a history of lung transplantation and chronic obstructive pulmonary disease, and (5) cancer patients who have/have not received chemotherapy. Since sepsis and ARDS are not easy to diagnose, two doctors will separately perform patient inclusion/exclusion criteria, extract the data, and assess the data quality. Any discrepancies will be resolved by consensus, and if necessary, a third professor can be consulted.

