### 2.4. Data Collection

All clinical data will be collected by investigators and trained personnel. Each participant’s data will be filled in electronic case report forms (CRF) and stored online using research electronic data capture (REDCap) [23]. The CRF is designed to collect the necessary information based on this study protocol. The detailed contents of CRF contain four main parts: (1) demographics and chronic disease history (including age, gender, smoking status, hypertension, diabetes mellitus, chronic lung disease and coronary heart disease), (2) laboratory tests and imaging examination (including routine blood, routine biochemistry, coagulation function, arterial blood gas analysis, blood culture, sputum culture, and ID of chest CT), (3) treatment process (including source of infection, anti-infection therapy, ventilator use or not, and type and dose of vasopressor therapy), (4) outcomes (intensive care unit (ICU) stay or not, length of ICU stay, total length of hospital stay, and in-hospital death).

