### 2.6. Outcome Measures

In this study, the primary outcome measure will be occurrence of ARDS, which is defined as pulmonary or nonpulmonary sepsis that had progressed into ARDS.

Secondary outcome measures are as follows:

(1)Grade of pulmonary damage: patients will be classified as mild (200 <  PaO2/FiO2 ≤ 300 mmHg), moderate (100 < PaO2/FiO2 ≤ 200 mmHg), or severe (PaO2/FiO2  ≤  100 mmHg) at the moment of diagnosis of ARDS [2];(2)Ventilator-free days, VFD: defined as the number of days between successful weaning from mechanical ventilation and day 28 after ICU admission;(3)Respiratory organ failure-free days, RFFD: defined as the number of days between a day without evidence of respiratory organ failure [27];(4)28-day mortality: all-cause mortality within 28 days following enrolment.

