Recently, artificial intelligence-based radiomics applied in predicting patients who are at risk of developing immunotherapy-induced pneumonitis and radiation pneumonitis have shown promising results [20,38]. Based on these findings, future studies could focus on comparing predictive values of different imaging approaches, such as CT, ultrasound and bronchoscopy combined with artificial intelligence technology. In this ambispective cohort study, we developed and validated a novel model incorporating radiomic signatures and clinical signatures to provide an easy-to-use and individualized prediction of SI-ARDS occurrence and severe degree in patients at early stage. Moreover, research has indicated that immune microenvironment abnormalities play a critical role in SI-ARDS [39,40], revealing that disturbances of neutrophil migration and neutrophil apoptosis caused neutrophil accumulation in the lung tissues, resulting in lung injury. We considered and initially explored correlation between radiomic features and immune-associated inflammatory indicators.

This study has several limitations. First, there are intrinsic limitations and possible patient selection bias in this observational and partly retrospective cohort study. Since the majority of sepsis patients first receive a chest X-ray, those with a relatively high risk of ARDS would be referred for chest CT and those with severe septic shock would receive bedside chest radiograph. However, a subgroup analysis will be performed by comparing mild sepsis group alone (removing the septic shock subgroup) with the pulmonary and non-pulmonary sepsis group. Second, the follow-up duration is relatively short. However, this period is quite adequate for consideration of the early primary outcome of SI-ARDS. A third limitation is the relatively small sample size and that high-dimensional extracted radiomics features may result in model overfitting. Therefore, these available data still remain inconclusive and need to be further validated in future multicenter prospective studies.

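### Freedom from low oxygenation is secured only before admission, not at the chest CT, so patients already in ARDS at the scan can enter the primary AUC as predicted cases

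*Protocol article*

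**What the plan says.** Section 2.2 lists five exclusions. The third is the only one directed at existing hypoxaemia and removes patients "whose oxygenation index (OI, arterial oxygen tension/inspired oxygen fraction [PaO2/FIO2]) ≤300 mmHg before admission". The same section gives the order of events for the outcome: "SI-ARDS is defined by sequential occurrence of the sepsis-3 consensus criteria for sepsis", followed by the Berlin definition for ARDS. One set of criteria covers both the developing and the validating group.

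Section 2.6 names as primary outcome "occurrence of ARDS, which is defined as pulmonary or nonpulmonary sepsis that had progressed into ARDS". The Abstract gives the horizon: "predicting in-hospital incidence of SI-ARDS".

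The predictor is the chest CT. Section 2.1 says that CTs of treated patients will be collected. It does not say which scan is used or when it must be taken. The case report form contents in section 2.4 include "blood culture, sputum culture, and ID of chest CT"; neither a scan time nor an ARDS onset time is among the listed items.

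The Introduction says of chest CT that it "is also a method for ARDS diagnosis based on characteristic radiologic features". The Discussion, under limitations, says that "those with a relatively high risk of ARDS would be referred for chest CT".

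**The concern.** A prediction study needs patients who are free of the outcome when the prediction is made. Here that moment is the scan, but the stated eligibility rule checks oxygenation at an earlier point, admission. Between the two, a patient can develop ARDS, be scanned, and remain eligible as a case.

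For such a patient the model recognises a condition that is already present. The Introduction itself says that ARDS has characteristic features on CT, so these cases are likely to be the easier ones. The Discussion justifies the study by the delay that follows once oxygenation has fallen and imaging findings are clear, and the model is useful only if it works before that point.

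The validation design would not reveal the problem. The 160 discovering and 40 testing patients come from the same 200 retrospective patients, and the 200 prospective patients enter under the same criteria. All the AUCs would mix recognition with prediction.

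**Working it through.** **1. Does any passage place the CT before ARDS?**

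| Place | What it orders | Is the CT in the sequence? |
|---|---|---|
| 2.2, exclusion (3) | OI above 300 mmHg up to admission | No |
| 2.2, SI-ARDS definition | Sepsis, then ARDS | No |
| 2.6, primary outcome | Sepsis, then ARDS | No |
| Abstract, outcome | ARDS during the hospital stay | No |
| 2.1 and 2.4, collection | None; CT collected and identified by ID | No time given |

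Together these fix that ARDS follows sepsis and occurs in hospital. They do not fix that it follows the scan. Retrospective recruitment covers May 2015 to August 2020, so for that half the scan times were set by routine care.

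**2. What could this do to the AUC?** The document gives no figure on this point, so there is none to reproduce. The effect depends on three unknowns, all assumed below:

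- f, the share of ARDS cases already in ARDS at the scan: 10% to 50%
- AUC_inc, the AUC for ARDS that begins after the scan: 0.65 to 0.75
- AUC_prev, the AUC for ARDS present at the scan: 0.85 to 0.95

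For a given score, the AUC is the probability that a random case scores above a random control. Both kinds of case are compared with the same non-ARDS controls, so the observed value is an exact mixture:

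AUC_obs = f × AUC_prev + (1 − f) × AUC_inc

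Overstatement = f × (AUC_prev − AUC_inc)

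| f | AUC_inc 0.75, AUC_prev 0.85 | AUC_inc 0.70, AUC_prev 0.95 | AUC_inc 0.65, AUC_prev 0.95 |
|---|---|---|---|
| 10% | 0.760 (+0.010) | 0.725 (+0.025) | 0.680 (+0.030) |
| 30% | 0.780 (+0.030) | 0.775 (+0.075) | 0.740 (+0.090) |
| 50% | 0.800 (+0.050) | 0.825 (+0.125) | 0.800 (+0.150) |

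The ends of the range are 0.10 × (0.85 − 0.75) = 0.01 and 0.50 × (0.95 − 0.65) = 0.15. A simulation with normally distributed scores, for 0.70 and 0.95, gave 0.725, 0.776 and 0.826 at f = 10%, 30% and 50%, in agreement with the middle column. If AUC_prev equals AUC_inc, the overstatement is 0 at every f.

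**3. In numbers of patients.** Section 2.3 cites an ARDS rate of 25–50%. In the 160 discovering patients that is 160 × 0.25 = 40 to 160 × 0.50 = 80 cases. Ten cases already in ARDS at the scan would then be 10/80 = 12.5% to 10/40 = 25% of all cases. With 0.70 and 0.95 the overstatement is 0.125 × 0.25 = 0.03 to 0.25 × 0.25 = 0.06. The ten is illustrative only.

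**The case against.** The strongest reply is that this argues from silence. The text is a condensed article. The full protocol is not shown, nor is the flow chart (Figure 1), and either may state the scan timing. The visible wording also leans towards new-onset ARDS: early prediction, incidence in hospital, sepsis that progressed. The Introduction names the identification of pulmonary or non-pulmonary sepsis as a use of CT before it mentions ARDS diagnosis, which suggests an early scan.

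Part of this stands. How the index scan is chosen could well be left to a fuller document. But the eligibility rule is not left out. It is stated, with a time anchor that does not fit the stated aim, and none of the wording about new onset involves the CT.

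Four stronger readings are tempting, and the document does not support them:

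- **That ARDS patients will in fact be scanned late and counted.** The text permits it; it does not show that it happens or how often.
- **That suspected ARDS triggers the scan.** The Discussion speaks of "those with a relatively high risk of ARDS would be referred for chest CT". Being at high risk is not having, or being suspected of having, ARDS. The passage shows that scanning depends on clinical risk, and the article offers it as a selection-bias limitation.
- **That the study CT decides the outcome.** The remark that CT "is also a method for ARDS diagnosis based on characteristic radiologic features" is general. Section 2.2 relies on the Berlin definition, with two doctors applying the criteria and extracting the data. The remark supports only the point that established ARDS can be visible on the predictor image.
- **That the outcome has no horizon.** The Abstract gives one, the hospital stay. What is missing is a starting point tied to the scan.

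**Conclusion.** The point holds in a conditional form. As written, exclusion (3) admits patients who are already in ARDS when the CT is taken, and they can count as predicted cases in the primary AUC in both cohorts. The AUC would then not measure early prediction alone. The expected bias is upward, because established ARDS has visible CT features.

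Its size is not known from the document. The range of +0.01 to +0.15 rests wholly on the assumed shares and AUCs, and zero remains possible. That the AUC is certainly inflated, or by any particular amount, is not shown. The conclusion would fall away if the flow chart or the full protocol already requires the scan to precede ARDS. In that case the article's eligibility wording should be brought into line with it.

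Because the point concerns what the primary performance measure means, it should be settled before the primary AUC is calculated.

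**What to change.** - Define one index CT per patient by a single rule applied to both cohorts, for example the scan from the sepsis work-up, and make it the time of prediction.
- Add the date and time of the index CT and of ARDS onset to the case report form.
- Restrict the primary AUC to patients who do not meet ARDS criteria at or before the index CT. Count as events only in-hospital ARDS with onset after it.
- Report patients already in ARDS at the scan as a separate stratum, outside the primary AUC.

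The stated in-hospital horizon can stay; no shorter window is needed to cure this defect.

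The cost is revised eligibility and outcome wording, two times taken from each record, and fewer patients and events in the primary analysis. If 25% of cases were in ARDS at the scan (an assumption), the 40–80 expected cases among the 160 discovering patients would fall to 40 × 0.75 = 30 to 80 × 0.75 = 60. The AUC will probably be less favourable, but it will refer to early prediction.
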